### Study-specific visits and procedures

The whole experiment for every participant will involve treatment with Bushen Culuan Decoction+ clomiphene citrate placebo or clomiphene citrate+ Bushen Culuan Decoction placebo for three menstrual periods or six menstrual periods (Fig. 1). Every participant will attend up to five visits, including the screening visit, baseline visit, treatment visit, end-of-treatment visit, and follow-up visit. The overview of the study visits is shown in Table 1. All concomitant medications and adverse events will be recorded at every visit.

**Table 1 Tab1:** Overview of study visits

Overview of study visits								
	Screening visit	Baseline visit	Treatment visit				End-of-treatment visit	Follow-up visit
			1st and 2nd menstrual period	3rd menstrual period	4th and 5th menstrual period	6th menstrual period		
Physical examination	√							
Basal body temperature		√	√	√	√	√	√	
Fasting blood sample for safety profile		√					√	
Urine routine test for safety profile		√					√	
ECG for safety profile		√					√	
Pregnancy test*		√	√	√	√	√	√	√
Fasting blood sample for sex hormone steroids		√		√		√	√	
Transvaginal ultrasound for ovulation monitoring		√	√	√	√	√	√	
Blood sample for AMH and INHB		√					√	
Transvaginal ultrasound		√					√	
Coagulation indicator		√					√	
Traditional Chinese Medicine symptom score**		√	√	√	√		√	
Pregnancy and neonatal record								
Query for adverse events and concomitant medications		√	√	√	√	√	√	

Physical examination: weight and height for BMI; acne and hair observation

Fasting blood samples for safety profile: RBC, Hb, WBC, PLT, ALT, AST, BIL, BUN, Cr

Urine routine test for safety profile: WBC-M, RBC-M, PRO

Pregnancy test: will be tested if the high-temperature phase of BBT continues for more than 14 days in a menstrual period, or the menstrual period is longer than 28 days

^*^Degree of importance

Fasting blood samples for sex hormones: FSH, LH, PRL, E_2_, P, T

Transvaginal ultrasound: uterine and bilateral ovarian volumes, endometrial thickness and type, ovarian volume, antral follicle count, and sizes of ovarian cysts or developing follicles. Peak-systolic flow velocity, PI and RI of uterus and ovaries

Coagulation indicator: PT, TT, APTT, FIB

Traditional Chinese Medicine symptom score is shown in Table 2

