### Treatment visit

After getting the medication package, every participant will start medical treatment on day 5 of the 1st menstrual period and visit the clinical investigator on day 25 of the 1st menstrual period or on day 1 of the 2nd menstrual period if the menstrual period duration is less than 25 days. In every treatment visit, relevant information about the participant will be recorded, and she will be given the medication package for the next menstrual treatment period.

In the 1st and 2nd menstrual periods, the participant will start to monitor ovulation every day from the 12th day of menstruation, and the size of the dominant follicle will be recorded. If there is ovulation, a urine pregnancy test will be performed to exclude pregnancy. If there is no pregnancy, the treatment will be continued in the next period. The detailed medication use status, the date and duration of the last menstruation period along with BBT, and ovulation monitoring results will be recorded, and the traditional Chinese medicine symptom score will be evaluated.

In the 3rd menstrual period, serum sex hormones at the ovulatory phase will be tested and recorded in addition to all information collected in the previous period. If there is no ovulation, the blood sample for sex hormone testing will be collected on the 15th day of the menstrual period.

After treatment for 3 periods, we will analyze the ovulation of every participant. The participant will be considered to have regained regular ovulation successfully if she had ovulation in all of the past 3 periods. The treatment of the participant will be terminated, and she will have an end-of-treatment visit and then move forward into the follow-up stage. If the participant ovulates fewer than 3 times, she will go into the second treatment cycle.

For every participant in the second treatment cycle, she will have a 4th, 5th, and 6th treatment visit. The procedures of the 4th and 5th treatment visits will be the same as those of the 1st and 2nd visits, and the 6th visit will be the same as that of the 3rd visit. After the 6th menstrual period treatment, all participants will stop treatment and move into the next stage regardless of whether they recover regular ovulation.

If the participant gets pregnant in the treatment process, she will stop the treatment immediately and move into the end-of-treatment visit and follow-up stage.

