### End-of-treatment visit

The information to be collected and the procedure will be the same as in the baseline visit, including general vital signs, safety index, and effectiveness index. If the participant is pregnant, the transvaginal ultrasound will be skipped. The clinical investigator will inform every unpregnant participant that she will be contacted by phone every 3 months to have a follow-up visit until she is pregnant or until 12 months after the end of treatment. If the participant is pregnant in the treatment or follow-up stage, phone follow-up will be continued until there is a pregnancy outcome.

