#### Secondary outcomes

Secondary outcomes are as follows:
Ovulation rate;Basal body temperature;Serum sex hormones: FSH, LH, PRL, E_2_, P, T;Serum AMH and inhibin B;Uterine and bilateral ovarian volumes at the early follicle phase;Thickness and type of endometrium at the early follicle phase;Antral follicle count and the size of dominant follicle;Peak-systolic flow velocity, pulsatility index, and resistance index of the uterus and bilateral ovaries;Serum coagulation indicators;Traditional Chinese medicine symptom score.

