#### Statistical analysis

An independent statistician will use SPSS 21.0 (SPSS, Chicago, Illinois, USA) to analyze the data.

The mean ± SD will be used to describe normally distributed data, while medians with IQRs will be used if the data are not normally distributed. The *χ*^2^ test will be used for evaluating differences between dichotomous variables, while one-way analysis of variance or Student’s *t* test will be used for evaluating continuous variables. The Mann-Whitney test will be used if the data are not normally distributed. A *p* value < 0.05 will be considered statistically significant.

If there are dropouts from the study, the last-observation-carried-forward principle will be used to compensate for the loss of data.

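### Every woman who conceives on treatment lacks an end-of-treatment value for the volume, endometrial, antral follicle and Doppler outcomes, so the planned unadjusted tests compare arms selected by on-treatment pregnancy

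*Protocol article*

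**What the plan says.** The Secondary outcomes section of the protocol article lists, among others, "Uterine and bilateral ovarian volumes at the early follicle phase", endometrial thickness and type, "Antral follicle count and the size of dominant follicle", and "Peak-systolic flow velocity, pulsatility index, and resistance index of the uterus and bilateral ovaries".

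Table 1 (Study-specific visits and procedures) has two ultrasound rows. The full scan is ticked at baseline and end of treatment only. Its footnote begins "Transvaginal ultrasound: uterine and bilateral ovarian volumes, endometrial thickness and type, ovarian volume, antral follicle count" and goes on to the flow indices. The other row is ovulation monitoring, ticked in every treatment period. For that scan the Treatment visit section says "the participant will start to monitor ovulation every day from the 12th day of menstruation, and the size of the dominant follicle will be recorded" and names no other measurement.

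A woman who conceives during treatment is covered by two rules. Under Treatment visit, "she will stop the treatment immediately and move into the end-of-treatment visit and follow-up stage". Under End-of-treatment visit, "If the participant is pregnant, the transvaginal ultrasound will be skipped".

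The Statistical analysis section plans Student's t test or one-way analysis of variance for continuous variables, or the Mann-Whitney test if they are not normally distributed. No covariate is named. Its only missing-data rule is "If there are dropouts from the study, the last-observation-carried-forward principle will be used to compensate for the loss of data".

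**The concern.** Whether these outcomes are observed depends on an event after randomisation, and that event is part of the primary outcome. The Objectives section asks whether the decoction gives a higher pregnancy rate than clomiphene. If it does during treatment, the decoction arm loses more women from these comparisons than the control arm.

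The loss is harmless only if conception is unrelated to what the scan measures. The Background assumes otherwise: it expects the pregnancy rate to rise through follicle development, ovulation and endometrial receptivity. If that mechanism is at work, the women missing from the end-of-treatment scan are not a random subset of either arm. The measures meant to show how the treatment works would then be compared between groups that randomisation no longer balances.

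**Working it through.** **Tracing the missing value.**

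1. The affected outcomes come only from the full scan at baseline and end of treatment (Table 1).
2. On-treatment conception leads directly to the end-of-treatment visit, where the scan is omitted. No post-baseline value exists.
3. Conception in follow-up happens after that visit, so the value exists and is kept.
4. Dominant follicle size is recorded in each period and is not lost in this way.
5. The carry-forward rule names dropouts. The Withdrawal criteria describe these as women no longer taking part in study procedures. A pregnant woman attends the end-of-treatment visit and is followed to the pregnancy outcome, so she does not fit. A t test or Mann-Whitney test on available values leaves her out.

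**Denominators.** The plan's 219 per group is reproduced with 90% vs 80%, power 0.90 and one-sided alpha 0.05: (1.645 + 1.282)² × 2 × 0.85 × 0.15 / 0.10² = 218.4, so 219. The total of 528 gives 264 per arm. These figures are used only for standard errors.

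**Assumptions.** The article gives no on-treatment pregnancy rate and no correlation between scan and conception. I assume 20% pregnant on treatment in the control arm and 30% or 40% in the decoction arm. I assume a correlation r of 0.3 to 0.5 between the scan measure (SD 1) and a normal latent tendency to conceive.

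**Comparison restricted to non-pregnant women.** With a fraction p pregnant and z the (1 - p) normal quantile, the mean among the remaining women shifts by -r × φ(z)/(1 - p).

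| p | z | φ(z) | φ(z)/(1 - p) |
|---|---|---|---|
| 0.20 | 0.842 | 0.280 | 0.350 |
| 0.30 | 0.524 | 0.348 | 0.497 |
| 0.40 | 0.253 | 0.386 | 0.644 |

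The bias is -r times the arm difference in the last column.

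- 30% vs 20%: -r × 0.147 = -0.04 (r = 0.3) to -0.07 (r = 0.5). A true 0.30 becomes 0.26 to 0.23.
- 40% vs 20%: -r × 0.294 = -0.09 to -0.15. A true 0.30 becomes 0.21 to 0.15.
- Equal rates: the terms cancel and the bias is zero.

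**Against the standard error.** Only scanned women count, and SE = √(1/n₁ + 1/n₂).

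- 30% vs 20%: 153 and 175 women (of 219 per arm) give 0.111; 185 and 211 (of 264) give 0.101. The bias is about 0.4 to 0.7 SE.
- 40% vs 20%: 131 and 175 give 0.115; 158 and 211 give 0.105. The bias is about 0.8 to 1.4 SE.

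**Carrying baseline forward for pregnant women.** The last scan is the pre-treatment one, so each contributes a change of zero. For change from baseline in SD units, a true difference d is estimated as (1 - p₁)d - r[φ(z₁) - φ(z₀)], where 1 is the decoction arm and 0 the control arm. For d = 0.30:

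- 30% vs 20%: 0.70 × 0.30 - r × 0.068 = 0.19 to 0.18.
- 40% vs 20%: 0.60 × 0.30 - r × 0.106 = 0.15 to 0.13.
- 20% in both arms: 0.80 × 0.30 = 0.24, so this rule shrinks the effect even when pregnancy rates are equal.

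**What baseline adjustment recovers.** I simulated 2,000,000 women per arm with no true effect and a baseline-to-follow-up correlation of 0.7, and analysed non-pregnant women only. At 30% vs 20% and r = 0.5 the unadjusted bias is about -0.07. Adjusted for baseline it is about -0.04 if conception follows the end-of-treatment value, about 0 if it follows the baseline value, and still about -0.07 if it follows only the part of the outcome unrelated to baseline.

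**The case against.** **No analysis plan is shown, and handling of pregnant women is commonly left to one.** This is fair as to the wording of the analysis. But the schedule, the skip rule, the outcomes and the tests are all fixed in this article, and a later plan cannot recover scans that were never made. It can only restrict, adjust or relabel the comparison.

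**The missing value cannot be avoided.** Volumes and endometrium are defined in the early follicular phase, which a pregnant woman does not have. This stands. Skipping the scan is a clinical matter and is not questioned; what can change is the analysis and how its result is described.

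**A reader might infer that all primary-outcome successes are removed.** The article does not support that. The primary outcome has no stated window, and non-pregnant women are followed for up to 12 months after treatment. Those who conceive then have already been scanned. Nor does the article say that pregnant women are excluded. That follows from its tests and from a carry-forward rule limited to dropouts.

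**A reader might infer that a working treatment will look harmful on these measures.** That needs unequal on-treatment pregnancy rates and a positive correlation across all six diseases. Under the article's diagnostic criteria a high follicle count or large ovarian volume counts towards PCOS, so more is not uniformly better, and signs may differ or partly cancel in the pooled comparison.

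**These are secondary outcomes.** True: the primary comparison, sample size and safety analysis are unaffected.

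**Conclusion.** The concern holds for on-treatment conceptions and for volumes, endometrial thickness and type, antral follicle count and Doppler indices. The planned unadjusted tests do not estimate a randomised treatment effect on these outcomes, and carrying the baseline value forward would not repair that.

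The likely distortion is modest: under one standard error at 30% vs 20% pregnant, and up to about 1.4 at 40% vs 20%. These figures rest on assumed pregnancy rates and an assumed correlation of one sign. The documents fix neither the size nor the direction. This is worth correcting before these results are reported, but it does not threaten the main conclusion of the trial.

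**What to change.** State in the analysis section that the end-of-treatment ultrasound outcomes:

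- are compared among women not pregnant at that visit;
- use no carry-forward for women who are pregnant;
- are adjusted for the baseline ultrasound value;
- are reported as descriptive, with the number pregnant per arm at that visit, and not as randomised treatment effects.

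The cost is a change of wording and one covariate from a scan already scheduled at baseline, so it remains possible after recruitment. The price is that these comparisons lose confirmatory standing. Baseline adjustment reduces the selection only as far as baseline itself relates to conception, so the descriptive label is still needed.

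Taking these measures at the ovulation-monitoring scans would not be a substitute. Those scans start on day 12, not in the early follicular phase for which volumes and endometrium are defined, and women already past those visits could not supply the values.

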### Follow-up visit

After the end-of-treatment visit, participants who are not pregnant will come to follow-up visits every 3 months. In each visit, we will record the date and duration of the last menstrual period, her pregnancy situation, and a simple questionnaire for traditional Chinese medicine symptoms. For participants who are pregnant already, we will keep in touch with them until there is a pregnancy outcome.

The pregnancy outcomes are divided into
Natural labor;Cesarean section;Biochemical pregnancy;Spontaneous abortion;Artificial abortion.

For (1) and (2), we will record the weight, height, head circumference, and Apgar score of the newborn. For (4) and (5), the precipitating factors and relevant medical report are required to be offered by the participant.

### Outcome measures

#### Primary outcome

The primary outcome is pregnancy rate (confirmed by serum β-HCG positivity).

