**Methods:**

This is a randomized, double-blinded, double-dummy, parallel, positively controlled, adaptive, multicenter clinical trial. All participants will be randomly allocated by a central randomization system to the treatment group or the control group in a 1:1 ratio. The treatment group will undergo a 14-day treatment with Bushen Culuan Decoction 13 g three times a day and a 5-day treatment with clomiphene citrate placebo tablets 50 mg once a day starting on day 5 of every menstrual period. The control group will undergo a 14-day treatment with Bushen Culuan Decoction placebo 13 g three times a day and a 5-day treatment with clomiphene citrate tablets 50 mg once a day from day 5 in every menstrual period. The whole treatment will last through 3 menstrual periods or 6 menstrual periods, depending on whether ovulation is regained in the first 3 menstrual periods. All statistical analyses will be performed in SPSS 21.0 (SPSS, Chicago, Illinois, USA), and a *p* value < 0.05 will be considered statistically significant.

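### The primary pregnancy rate has no time window, and both windows the plan could imply are three menstrual periods shorter for women who ovulate well

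*Protocol article*

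**What the plan says.** Under Primary outcome: "The primary outcome is pregnancy rate (confirmed by serum β-HCG positivity". No time point follows, and no other section says which pregnancies enter the rate.

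The abstract makes treatment length depend on response: "The whole treatment will last through 3 menstrual periods or 6 menstrual periods, depending on whether ovulation is regained in the first 3 menstrual periods". Treatment visit gives the rule for stopping, "The participant will be considered to have regained regular ovulation successfully if she had ovulation in all of the past 3 periods", and for continuing, "If the participant ovulates fewer than 3 times, she will go into the second treatment cycle". Interventions describes the same two-cycle scheme.

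End-of-treatment visit says that women who are not pregnant are followed "until she is pregnant or until 12 months after the end of treatment". It foresees pregnancies in both the treatment and the follow-up stage. Statistical analysis plans a χ² test for dichotomous variables and mentions no allowance for time at risk.

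Ovulation rate is a secondary outcome. The Background hypothesises that the decoction raises the pregnancy rate partly by promoting ovulation. It also cites earlier trials of traditional Chinese medicine in which ovulation rates did not differ significantly between groups.

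**The concern.** A pregnancy proportion compares two arms fairly only if every woman has the same scheduled time in which a pregnancy can count. Here that time is set after randomisation, by ovulation, which the treatments are meant to change. The article offers two natural end points, end of treatment and end of follow-up. Each falls three periods earlier for a woman who ovulated three times out of three.

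If one arm restores ovulation better, more of its women stop early and that arm has less time to accumulate pregnancies. A plain comparison of proportions then understates its advantage. By the trial's own hypothesis, the arm penalised could be the decoction arm.

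The missing window also leaves open which pregnancies count at the interim, where diseases are selected on the pregnancy rate.

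**Working it through.** **Scheduled opportunity.** With 28-day cycles (an assumption), three periods last 84 days and six last 168 days, about 2.8 and 5.5 months. Adding 12 months gives about 14.8 v 17.5 months.

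**Inputs.** The article gives no ovulation or conception rate per cycle, and no figure of its own to reproduce on this point. Assumed:
- ovulation probability per period, *q*: 0.8 v 0.6, with smaller, shifted and zero gaps as checks;
- conception probability per ovulatory period, *f*: 0.10 and 0.15, the same in both arms;
- independent periods, no dropout, and *q* and *f* unchanged after treatment stops;
- 12 post-treatment periods standing for the 12 months.

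**Formulas.** Let *r* = 1 − *qf*, the chance of not conceiving in a period. Let *S* = [*q*(1 − *f*)]³, the chance of ovulating three times without conceiving and so stopping at period 3.
- Six common periods: 1 − *r*⁶
- End of treatment under the rule: 1 − *r*⁶ − *S*(1 − *r*³)
- Common 6 + 12 periods: 1 − *r*¹⁸
- End of follow-up under the rule: 1 − *r*¹⁸ − *S r*¹²(1 − *r*³)

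**Worked case, *f* = 0.10.**
- *q* = 0.8: *r* = 0.92, *r*³ = 0.7787, *r*⁶ = 0.6064, *S* = 0.72³ = 0.3732. Six common periods: 39.4%. End of treatment: 0.3936 − 0.3732 × 0.2213 = 31.1%.
- *q* = 0.6: *r* = 0.94, *r*³ = 0.8306, *r*⁶ = 0.6899, *S* = 0.54³ = 0.1575. Six common periods: 31.0%. End of treatment: 0.3101 − 0.1575 × 0.1694 = 28.3%.

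**Difference between arms, in percentage points:**

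| Ovulation | *f* | Six common periods | End of treatment | Common 6 + 12 | End of follow-up |
|---|---|---|---|---|---|
| 0.8 v 0.6 | 0.10 | 8.4 | 2.8 | 10.5 | 8.8 |
| 0.8 v 0.6 | 0.15 | 10.3 | 3.6 | 8.3 | 7.2 |
| 0.75 v 0.65 | 0.10 | 4.2 | 1.4 | 5.2 | 4.4 |
| 0.75 v 0.65 | 0.15 | 5.2 | 1.8 | 4.1 | 3.6 |
| 0.9 v 0.7 | 0.10 | 7.9 | −0.3 | 8.8 | 6.6 |
| 0.7 v 0.7 | either | 0 | 0 | 0 | 0 |

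**Variation between women.** Letting *q* vary between women (beta distribution with parameters summing to 2, means 0.8 and 0.6, *f* = 0.15) gives 38.6% v 34.1% at end of treatment, a difference of 4.5 points. Over six common periods it gives 52.4% v 41.3%, a difference of 11.1 points. With the 12 post-treatment periods counted, the difference is 11.2 under the rule against 12.1 with common follow-up, a loss of 0.9 points.

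**The case against.** Four points on the other side carry weight.

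**The bias is conditional.** With equal ovulation it is zero under every window, and the Background cites earlier trials with no significant difference in ovulation. A reader might infer that the comparison is certainly biased; the article does not support that. The trial's own hypothesis, however, names ovulation as a route of effect, so the condition cannot be assumed away.

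**Every non-pregnant woman gets the same 12 months after treatment.** If those months count, most of the distortion goes. This stands, but nothing says that they count.

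**Reversal of the result is not shown.** The tempting claim is that its direction is at stake. The calculations show attenuation, and the one negative value, −0.3 points, amounts to no difference.

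**This is a condensed article.** A window may stand in the full protocol. But the stated treatment rule and follow-up anchor give unequal time under either end point the article offers, so this is more than an omitted detail.

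Two further inferences should not be drawn. The urine test at treatment visits ("If there is ovulation, a urine pregnancy test will be performed to exclude pregnancy") does not contradict a serum-confirmed outcome, since a screen can precede confirmation. Nor need telephone contact conflict with "participants who are not pregnant will come to follow-up visits every 3 months", since a call may arrange the visit. It also cannot be said that the interim would come too late: that requires even, uninterrupted recruitment while first-stage data mature, which Sample size estimation does not state.

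**Conclusion.** The point holds in conditional form. The primary outcome has no window, and under either available end point women who ovulate in all three periods have three fewer periods in which a pregnancy can count. If ovulation differs by arm, the bias runs against the better-ovulating arm.

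At an assumed 80% v 60% ovulation and 10–15% conception per ovulatory cycle, about 8–11 points over six common cycles becomes about 3–5 points at end of treatment. If the 12-month follow-up counts, the loss is about 1–2 points. A smaller ovulation gap gives a smaller loss, and no gap gives none. These sizes rest on assumed rates and on ovulation persisting after treatment stops. The inequality in scheduled time rests on the article's text alone.

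**What to change.** Define the primary outcome as the proportion of all randomised women with a serum β-HCG-confirmed pregnancy conceived within one fixed calendar period from randomisation. Make that period the same whether a woman stops at period 3 or period 6, and long enough to cover six periods. Since eligible women include those with long cycles or amenorrhoea, six 28-day cycles (168 days) would be too short for some. Use the same window at the interim and final analyses, and report later pregnancies as a secondary outcome. Leave the treatment rule unchanged.

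State that every positive urine or self-reported test in the window, including those reported at follow-up contacts, is confirmed by serum β-HCG.

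The cost is protocol and analysis-plan wording, plus a serum test for each positive report not already confirmed. The existing three-monthly contacts already reach early stoppers. There is one small downside: early stoppers are contacted every three months while continuers are seen every period, so very early losses may be detected less often in early stoppers. A sensitivity analysis excluding biochemical pregnancies, which Follow-up visit already lists as a recorded outcome, addresses this.
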